**Fig. 1 fig1:**
[figure not shown]
Study participation flow diagram GPs: general practitioners; PTs: physiotherapists; Pink: related to GPs; Blue: related to PTs; Green: related to patients.

Physiotherapists practicing in the geographical area of intervention clusters will be recruited after cluster randomization through GP referral, direct contact by the research team, and professional social media channels. Occupational therapists will be recruited from interdisciplinary management clinics affiliated with the study network.

#### Patients

2.4.2

Patient recruitment will occur after cluster randomization of clinicians, with patients allocated according to their GP's study arm. All patients consulting a participating GP for LBP will be screened during the first consultation and provided with study information. Eligible patients who consent will enroll by scanning a QR code, which triggers baseline questionnaires and notifies the research team. The research team will then contact patients by phone to confirm understanding of study procedures and address questions. Patients who withdraw consent following this contact or fail to complete baseline questionnaires will be considered screening failures and excluded, with all collected data deleted.

To prevent and monitor selection bias, objective enrolment criteria will be provided to GPs in advance, and GPs will be asked to log all screened patients using the QR code, including reasons for non-inclusion. Practices will receive CHF 30 per included patient to support administrative workload, and regular monitoring of recruitment will be conducted to support enrolment and assess selection bias.

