**Fig. 2 fig2:**
[figure not shown]
Care Pathway SBT: Start Back Tool; GP: General practitioner; PT: physiotherapist; OT: occupational therapist.

GP training is delivered at the cluster level during quality-circle meetings, while physiotherapists complete a two-day workshop prior to delivering the intervention. Patient education and pathway-based care are initiated during the GP consultation, with escalation based on risk of chronicity criteria. Full details of the intervention and implementation strategies are reported in a TIDieR checklist (Supplementary Material S1), with detailed descriptions of GPs and physiotherapists training provided in Supplementary Materials S2 and S3.

Between 6 weeks and 3 months after the start of patient recruitment, GPs in the intervention group will be contacted by email to provide feedback on the intervention. All modifications will be documented and reported. Adaptations are anticipated to be minor and operational (e.g., timing of reminder emails, interprofessional communication procedures) and do not constitute changes to the clinical content of PRIME, the randomization scheme, or the primary outcome definitions. A formal adaptive trial design was not adopted, as the scope of planned adaptations does not require pre-specified interim analyses or sample size re-estimation.

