Adverse events (AEs) will be monitored through both passive and active surveillance. Passive surveillance involves continuous self-reporting by participants to the research team or their treating GP. Active surveillance is conducted through REDCap, where participants are prompted to report health events; any declaration triggers an automated alert to the research team for evaluation. Serious AEs are defined as events resulting in death, hospitalization or in persistent disability and are not anticipated given the non-invasive, non-pharmacological nature of the intervention. The expected non-serious AE is a fluctuation or increase in back or leg pain symptoms; this type of event is sometimes referred to as a normal reaction and will not be reported by GPs or physiotherapists.

Healthcare professionals baseline data will include general characteristics such as age, gender, years of clinical experience, practice setting and type, and prior training in LBP management. Patient baseline data will include demographics and social determinants of health. Participants will receive online questionnaire links by SMS and email. To limit participant burden, baseline data will be collected over two timepoints: on the day of the initial GP consultation and two days later. Follow-up assessments will occur at 10 days, 6 weeks, and 3, 6, 9, and 12 months (Supplementary Material S4). To promote retention, non-respondents will receive up to three reminders, followed by telephone contact if needed. Participants may receive financial compensation of up to CHF 50 based on questionnaire completion.

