For patient-level primary outcome, an exploratory non-inferiority analysis will be performed using a margin of −2.5 points on the RMDQ, reflecting the possibility that the intervention may be acceptable if non-inferior and cost-saving. Pre-planned mediation analyses will examine the role of psychological factors in patient outcomes [70]. Different secondary analyses will be conducted, including the number of participants in each group that reach 30%, 50% and 70% of improvement on the RMDQ, as well as the number of participants reaching the patient acceptable symptom state (≤4 on RMDQ) [71]. All analyses will be performed using SAS (version 9.4) and Stata or R. Deviations from the statistical analysis plan will be documented and reported.

Given the three primary outcomes operating at distinct and complementary levels (system, practitioner, patient), findings will be interpreted jointly but are considered complementary rather than causally dependent. Each outcome is analyzed and reported independently, without formal alpha correction across levels. Discordant findings across levels are anticipated and theoretically meaningful: the three outcomes cover different domains serving different decision-making purposes, consistent with the GRADE Evidence to Decision framework [72].

Participants who withdraw or fail to complete baseline questionnaires will be considered screening failures and excluded from the trial. To ensure sufficient power at the primary endpoint, recruitment will continue until at least 200 patients per group have completed the 6-month assessment; consequently, total recruitment may exceed 500 participants. GP dropouts during the study period will not result in patient exclusion. Patient outcomes will be analyzed according to the cluster allocation at enrolment *(intention-to-treat principle)*.

For cost-effectiveness analyses, missing cost data will not be imputed; instead, they will be complemented where available with health insurance records. In case of discordance between data sources, patient questionnaire data will be considered primary and insurance data will be used for validation and to complement missing values. For outcomes other than costs, multiple imputation assuming data Missing at Random will be performed using SAS PROC MI for variables with more than 10% missing data, incorporating covariates, intervention group, and cluster information.

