Several risks and limitations should be considered. First, patient recruitment is led by GPs, which may introduce selection bias despite mitigation strategies. Second, recruitment may also be challenging given GP workload, even though we included a high number of GPs in the study and developed recruitment strategies with a low time burden. If recruitment targets are not achieved, the recruitment period may be extended and additional eligible clusters may be recruited. If the final sample size remains below target, this will result in greater imprecision of the effect estimates and an increased risk of type II error, which will be acknowledged in the limitations. Third, the geographically limited setting increases the risk of contamination, particularly if patients in the control group consult trained physiotherapists. This will be monitored through patient questionnaires that will capture whether control-arm participants consulted a PRIME-trained physiotherapist. In such cases, sensitivity analyses will be conducted to assess the impact on primary outcomes. GP-level contamination is minimized by excluding GPs from the same practice who belong to different quality circles, and by restricting intervention materials (training content, digital tools, reminder emails) to intervention clusters only. The risk that control GPs will be passively exposed to intervention components in a meaningful way is low, and the risk that any exposure leads to important practice change to be even less [19]. Fourth, baseline data were collected after the initial GP consultation, which may limit evaluation of early consultation effects. Fifth, although LBP prevalence in primary care is not known to vary substantially by season, temporal factors such as GP availability during holiday periods or staggered training schedules could influence recruitment rates. Cluster-level recruitment monitoring will be conducted throughout the enrolment period. Finally, the effectiveness of complex behavioral interventions depends on fidelity and engagement, which may vary across clinicians, and co-interventions cannot be fully controlled. Accordingly, this trial primarily evaluates the effectiveness of interventions targeting healthcare professionals rather than individual clinical encounters.

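### Enrolled patients who miss the baseline questionnaires are excluded and their data deleted, although this happens after allocation and first exposure; the exclusion could differ by arm and conflicts with the stated intention-to-treat analysis

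*Protocol article*

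**What the plan says.** Section 2.4.2 (Patients) fixes the order of events: "Patient recruitment will occur after cluster randomization of clinicians, with patients allocated according to their GP's study arm". Entry comes next: "Eligible patients who consent will enroll by scanning a QR code, which triggers baseline questionnaires and notifies the research team". A phone call from the research team follows. Patients who withdraw consent after that call are removed, and so are those who "fail to complete baseline questionnaires will be considered screening failures and excluded, with all collected data deleted".

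Section 2.6 (Outcomes) splits the baseline assessment: "baseline data will be collected over two timepoints: on the day of the initial GP consultation and two days later". Section 2.5.1 (Intervention group) places the start of PRIME at the same visit: "Patient education and pathway-based care are initiated during the GP consultation". The Discussion accepts the order but treats it only as a measurement limit: "baseline data were collected after the initial GP consultation, which may limit evaluation of early consultation effects".

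Section 2.12 (Statistical methods) repeats the exclusion: "Participants who withdraw or fail to complete baseline questionnaires will be considered screening failures and excluded from the trial". The same paragraph says that patients are analysed by their cluster's allocation at enrolment, on the intention-to-treat principle.

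**The concern.** Requiring a complete baseline before entry does no harm when baseline precedes randomisation. Here it follows randomisation, consent, enrolment and the first consultation with a GP who knows the arm. Whether a patient returns the forms is then behaviour that the consultation may influence, for example through reassurance, the educational material or satisfaction with the GP. Calling these patients screening failures takes them out of the analysis set without counting them as losses.

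Deletion makes this irreversible. Without their data nobody can compare the excluded patients between arms, impute for them or run a sensitivity analysis. All three primary outcomes are estimated on the patients who remain, so each is open to the same selection. The Discussion already lists GP-led recruitment as a source of selection bias; this rule adds a second one, which it does not list.

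**Working it through.** **The order of events.** Setting the sections side by side:

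1. Clusters are randomised (2.4.2, 2.9).
2. The patient sees the GP, and PRIME or usual care starts (2.5.1).
3. The patient consents and enrols by QR code, which triggers the questionnaires (2.4.2).
4. Baseline is collected that day and two days later (2.6).
5. Non-completers are excluded and their data deleted (2.4.2, 2.12).

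Step 5 removes people who are already enrolled at step 3, whereas section 2.12 analyses by allocation at enrolment. The two statements do not fit together. Table 2 (section 2.7) also lists items under a second baseline time point that ask about the consultation itself: use of the booklet, reassurance by the physician, and beliefs about back pain. That form is not a pre-exposure measure.

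**Scale, from the plan's own inputs (section 2.8).** There are 10 clusters per arm, 20 analysed patients per cluster, SD 6.0, ICC 0.05 and a target difference of 2.5.

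- Design effect = 1 + (20 − 1) × 0.05 = 1.95.
- Effective n per arm = 200 / 1.95 = 102.6.
- Standard error of the contrast = 6.0 × √(2 / 102.6) = 0.84.
- Power from a noncentral t with 18 df = 80.6%, against 80.97% stated. This reproduces closely.
- Total = 400 / 0.80 = 500, as stated.

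None of these figures changes. Section 2.12 continues recruitment until 200 patients per group complete 6 months, so excluded patients are replaced. The issue is bias, not power.

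**Bias formula.** Let q be the share excluded in an arm and D the amount by which excluded patients' 6-month RMDQ exceeds that of retained patients. The full mean equals the retained mean + qD, so the retained mean equals the full mean − qD. The shift in PRIME minus control is −D × (q in PRIME − q in control). The protocol gives neither q nor D; every value below is an assumption.

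| q PRIME | q control | D (points) | Shift (points) |
|---|---|---|---|
| 10% | 5% | 3 | −0.15 |
| 15% | 5% | 3 | −0.30 |
| 5% | 10% | 3 | +0.15 |
| equal | equal | same in both arms | 0 |

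Sizes of 0.15 and 0.30 are 6% and 12% of the 2.5-point target (0.15 / 2.5 and 0.30 / 2.5), or about 0.18 and 0.36 standard errors (0.15 / 0.84 and 0.30 / 0.84).

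**Wider range.**

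- 5% against 10%, D from 2 to 6: 0.05 × 2 = 0.1 to 0.05 × 6 = 0.3 points.
- A 10-point gap in rates (5% against 15%, or 10% against 20%), D from 2 to 6: 0.2 to 0.6 points.
- Equal rates of 5 to 10%, but opposite kinds of patient lost (D of 2 to 4 with opposite signs): 2 × 0.05 × 2 = 0.2 to 2 × 0.10 × 4 = 0.8 points.
- Imaging, D of 20 to 30 percentage points and a rate gap of 5 to 10 points: 0.05 × 20 = 1 to 0.10 × 30 = 3 percentage points, against a 15-point target.

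**The case against.** The best defence is that nothing shows the loss to be differential, and that the plan has features which limit it. Patients are not told their arm (2.10). The research team phones everyone who scans the code (2.4.2). Non-respondents get up to three reminders and then a call (2.6), although this is stated for retention and not specifically for baseline. The assumed shifts are well under one standard error, and adjustment for baseline variables would remove any part that those variables explain among the patients retained. Patients who skip baseline may also supply little later data, and imputation under missing at random will not cure selection that depends on the outcome itself. All of this stands, and it limits how much should be claimed.

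Four stronger readings are tempting and are not supported:

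- A reader might infer that the exclusion is arm-dependent. The text shows only that it could be, as no rates are given.
- A reader might infer that nothing could be checked. The QR scan notifies the team, GPs are asked to log screened patients with reasons for non-inclusion, and recruitment is monitored for selection bias (2.4.2), so counts by arm may survive. The GP log, however, concerns non-inclusion at screening and not a form missed later. The CONSORT sentence in 2.3.2 refers to all post-randomisation exclusions, but it was written about spinal pathology.
- A reader might take the day-2 trigger as an explicit rule. It is inferred from the plural in 2.4.2 and the two-part baseline in 2.6.
- A reader might take the mention of withdrawal in 2.12 to cover withdrawal at any time. Since it speaks of screening failures, it is more naturally a loose repeat of 2.4.2.

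The defence does not answer the main point. Data protection can justify deletion when consent is withdrawn, but the rule applies the same deletion to mere non-completion.

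**Conclusion.** The point holds as a design flaw that should be corrected, not as a demonstrated bias. The protocol excludes enrolled patients after allocation and first exposure, which contradicts its own intention-to-treat statement, and then deletes what would be needed to judge the consequence. Direction and size are unknown. The working figure of 0.15 to 0.30 RMDQ points rests on assumed exclusion of 10 to 15% against 5% and an assumed 3-point gap; the wider assumptions run from 0 to 0.8 points. The case rests on the step being avoidable and irreversible, not on a large expected effect. That only the day-2 form need be missed is the natural reading, not stated text.

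**What to change.** In sections 2.4.2 and 2.12:

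- Keep every patient who consents and enrols, and does not withdraw consent, in the trial and the intention-to-treat set, whether or not the baseline forms are complete, and follow them up as planned.
- Handle missing baseline values by the planned multiple imputation. Section 2.12 restricts this to variables with more than 10% missing; say that baseline covariates are imputed below that level too, or these patients would drop out of the adjusted models.
- Delete data only when a patient withdraws consent and asks for deletion.
- Report baseline non-completion and early withdrawal by arm in the CONSORT diagram.
- Give the same timing of withdrawal in 2.12 as in 2.4.2.

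The cost is a protocol amendment, which under section 2.14 needs ethics approval before use if it is substantial, a changed data-handling rule, and some patients with missing baseline data. The plan should also say whether such patients count towards the 35-patient cluster limit and the payment per included patient. The sample-size calculation is unchanged. Because deleted data cannot be restored and recruitment was planned from February 2026, deletion for non-completion should stop as soon as the amendment allows.

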### Interventions

2.5

#### Intervention group

2.5.1

PRIME is a multilevel intervention designed to promote guideline-concordant, high-value care for LBP in primary care. It comprises core clinical components targeting GP consultations, physiotherapy management, interdisciplinary rehabilitation, and patient education, supported by various implementation strategies (Table 1). It was developed in accordance with the Medical Research Council guidance for complex interventions [25]. Content and intervention components were informed by international clinical guidelines [3,4,32], systematic reviews [15,17,29,33], and evidence from clinical trials [34,35] addressing low back pain management in primary care. The intervention was co-developed by a multidisciplinary research team in collaboration with GPs, physiotherapists, and occupational therapists to ensure clinical relevance and feasibility [25]. PRIME was piloted in primary care, and qualitative feedback from clinicians was used to refine intervention components and delivery procedures prior to this trial (in publication).

**Table 1 tbl1:** Multilevel intervention.

	Core clinical components	Implementation strategies
**GPs**	**GP (first) consultation(s)** EXPLORE • Risk factor of chronicity • Perform a physical exam • Use active listening EXCLUDE emergency cases during the first consultation • Infection • Osteoporotic fracture • Severe neurological issues EXPLAIN - REASSURE • Build confidence in movement • Keep explanations simple • Use educational resources* • LBP Booklet • Website for patients PRESCRIBE • Recommend movement and gradual return to activities • Work absence to a minimum If needed: • Physiotherapy • Medication	2 x 1-h interactive training during two remunerated quality circle meetings, facilitated by opinion leader. For each hour, GPs received 200CHF. In addition: • Between-training practice • Intervention manual • Website for GP • Patient videos Monthly reminders Patient education resources*
	**Clinical pathway recommendations** At 10 days and 6 weeks, clinical pathway recommendations are based on SBT level of risk and capacity to work, as well as PT reports if the patient has already started PT.	Automatic emails at 10 days and 6 weeks. Leaving choice and responsibility to GP in conjunction with PRIME
**PTs**	**Management strategies** EXPLORE • Explore beliefs • Explore motor behaviour • Validate and build relationship EXPOSE • Movement strategies modifications • Gradual exposition to feared movements and activities • Exercise variation EXPLAIN • Patient centered explanation • Check the understanding (teach back method) • Shared decision on objectives EMPOWER • Increase load and progressive exercises • Physical activity self-management • Management of flare-up	2 × 1 day workshop, facilitated by opinion leader, including: • Between-training practice • Intervention manual • Website for PT • Patient videos • Supervised treatment with simulated patients Follow-up online session Checklist for self-assessment Leaving choice and responsibility to PT (they are free to integrate other approaches in conjunction with PRIME)
**IR**	**Assessment of risk factors** • One-two individual sessions with a specialized OT to confirm the need for IR and provide target education • Rehabilitation program: individual and group sessions with OTs and PTs, focusing on education and active exercises.	GP training and resources to facilitate access to IR if needed.

Core components of PRIME include (1) training for GPs to support evidence-based assessment, reassurance, and risk-stratified care [23,33]; (2) training for physiotherapists to deliver biopsychosocial, guideline-concordant rehabilitation that target risk factors of chronicity [[36], [37], [38]]; (3) structured patient education resources [35,39,40]; and (4) a stepped clinical care pathway supported by automated decision support linked to patients’ risk of chronicity and interprofessional communication, including access to trained physiotherapists and interdisciplinary rehabilitation if needed (Fig. 2) [41,42]. Implementation strategies include interactive training sessions, educational materials, reminders, and automated clinical decision support tools.

**Fig. 2 fig2:**
[figure not shown]
Care Pathway SBT: Start Back Tool; GP: General practitioner; PT: physiotherapist; OT: occupational therapist.

GP training is delivered at the cluster level during quality-circle meetings, while physiotherapists complete a two-day workshop prior to delivering the intervention. Patient education and pathway-based care are initiated during the GP consultation, with escalation based on risk of chronicity criteria. Full details of the intervention and implementation strategies are reported in a TIDieR checklist (Supplementary Material S1), with detailed descriptions of GPs and physiotherapists training provided in Supplementary Materials S2 and S3.

Between 6 weeks and 3 months after the start of patient recruitment, GPs in the intervention group will be contacted by email to provide feedback on the intervention. All modifications will be documented and reported. Adaptations are anticipated to be minor and operational (e.g., timing of reminder emails, interprofessional communication procedures) and do not constitute changes to the clinical content of PRIME, the randomization scheme, or the primary outcome definitions. A formal adaptive trial design was not adopted, as the scope of planned adaptations does not require pre-specified interim analyses or sample size re-estimation.

